### Inclusion criteria

• All patients 55 years of age or over presenting to their GP with new onset symptoms of breathlessness, lethargy, or ankle oedema of over 48 hours duration, with no obvious recurrent, acute or self-limiting cause

• Able to give informed consent

### Exclusion criteria

Patients will be excluded if any of the following criteria are met:

• Known pre-existing HF or LVSD of any cause. However, patients with a pre-existing label of HF but without objective evidence (i.e. echocardiography) of this will not be excluded

• Severe symptoms requiring urgent assessment or stabilisation (e.g. breathless at rest, hypotension, confusion)

• Obvious clinically determined alternative diagnoses such as chest infection, exacerbation of chronic obstructive pulmonary disease or asthma

• Recent acute coronary syndrome (within 60 days)

• Major co-morbidity or other alternative diagnoses of no obvious acute and self-limiting cause (e.g. malignancy, severe respiratory disease, renal dialysis, mental health problem)

• Unable to provide informed consent

### Patient recruitment

GPs will give patients a written study information sheet that outlines the nature of the study, including possible benefits and risks, ethics approval, and advice that they can decline to participate or withdraw at any time without this affecting their medical care. GPs will then obtain verbal consent; full informed written consent will be taken subsequently by a research nurse at one of our two research assessment clinics. The flow of patients through the study is shown in Figure 1.

**Figure 1 F1:**
[figure not shown]
Flow of patient recruitment and data collection.

### Referral of patients to research assessment clinics

GPs will refer all eligible patients who have given verbal consent to participate in the study to one of our two research assessment clinics in two ways by: 1) asking the patient to telephone our research team administrator to arrange an appointment within seven days of the initial GP consultation, or the GP obtains patient contact details for entry onto the GP electronic database and the study team telephones the patient; and 2) GP completion of eligibility criteria onto the web-based Case Report Form will act as a referral letter, which we shall check to confirm eligibility and to ensure that the patient has contacted the research assessment team. If a patient changes their mind between agreeing to participate at the GP consultation and before attending their appointment at the research clinic, they are advised that they can cancel by telephoning either the research team or their GP. The patient can then re-consult with their GP, if necessary. Patients who decline to take part in the study will be managed as usual practice by GPs. When eligible patients decline to participate in the study or patients do not meet entry criteria for the study, GPs will complete a weekly electronic notification form of these details. These data will be used to assess potential selection bias.

### Recruitment rate

A total of 500 patients will be recruited, 25 per practice. To allow for delays, the target recruitment rate will be three patients per practice per month, with expected recruitment completed within 18 months. We shall monitor recruitment rates and if we fail to achieve the target accrual rate, additional practices will be invited to participate.

### Clinical decision rule

The CDR, developed from our HTA individual patient data and meta-analysis [40], intended to be used at the start of the diagnostic pathway in primary care [43], states:

Refer straight for echocardiography if the patient has any one of:

• A history of Myocardial Infarction

• Basal crepitations

• Ankle oedema in a male

Otherwise, carry out a BNP (or NT-proBNP) test and refer straight for echocardiography if BNP/NT-proBNP level is above one of three cut-offs set by gender/symptoms recorded in the clinical rule:

• Female without ankle oedema, refer if BNP > 210-360 pg/ml depending upon local availability of echocardiography (or NT-proBNP > 620-1060 pg/ml), or

• Male without ankle oedema, refer if BNP > 130-220 pg/ml (or NT-proBNP > 390-660 pg/ml), or

• Female with ankle oedema, refer if BNP > 100-180 pg/ml (or NT-proBNP > 190-520 pg/ml).

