Our study will build upon the current evidence and address the weaknesses in previous work. We have validated the CDR on primary care data sets but further validation in a symptomatic population in the real-life clinical setting is now indicated. Further exploration of the optimal NP cut-offs and further modelling of cost-effectiveness is also needed. We aim to prospectively validate the CDR in this study but GPs will not apply the CDR (applying the rule would be appropriate in an implementation study); GPs will refer all patients suspected of having HF and not previously diagnosed with Echo and we shall collect data on how well the CDR predicts the diagnosis of HF. The CDR’s impact potential will be demonstrated by evaluating whether its sensitivity and specificity is superior to that of GPs’ (unaided) decisions. Given the risk of delayed diagnosis of HF, GPs do not have clear guidance on whom to refer for further evaluation. Improving the ability of GPs to appropriately identify patients suspected of having HF is crucial not only to avoid unnecessary hospital admissions and reduce patient burden, but also to improve the quality of care for patients presenting to primary care with suspected HF.

We propose the following objectives:

1. To prospectively validate the performance of the CDR and compare it to using a natriuretic peptide assay alone on the diagnostic accuracy of HF in primary care

2. To determine if the CDR, or natriuretic peptide assay can be used in routine clinical practice to establish referral on for echocardiography in patients presenting with symptoms suggestive of HF

3. To quantify the most reliable cut-off levels of the natriuretic peptide assay in a group of symptomatic presenting patients

4. To model the cost-effectiveness of using the CDR in primary care

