### Blood collection and biomarker assessment

We shall collect a 30ml blood sample by venepuncture into EDTA K2 blood tubes to perform a point of care NT-proBNP test using a Cobas h 232 Reader and Roche Diagnostics CARDIAC proBNP test strips, for immediate results, and to perform a serum creatinine test to exclude renal dysfunction and calculate an eGFR (serum profile). Blood samples will be sent to Midlands Pathology for spinning and storage for batch analysis, and stored at −80°C for future analysis.

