### Sample size

Thirty urban and rural general practices in the West Midlands will be asked to participate to recruit 500 symptomatic patients. A search of routine practice morbidity data suggest that in a practice of 6,000 patients, around 60 patients over age 55 per year will present with new onset breathlessness. Breathlessness is the commonest of the three most likely symptoms of heart failure (others are lethargy or ankle swelling) and therefore these estimates on the rate that symptoms present will be the minimum rates. Assuming a 60% response rate then it would take at least nine months to recruit at least 25 such patients per practice. All practices will stop active patient recruitment at the end of 18 months. Calculations are based on sensitivity of 94% and specificity of 48% obtained from application of the CDR in our HTA funded individual patient data meta-analysis [40] and the prevalence of heart failure in a symptomatic population of 30%. A sample size of 500 patients with HF symptoms will therefore be sufficient to estimate the sensitivity of the CDR to within 4% and specificity to within 6% at the 95% confidence level.

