### Statistical analysis

Data will be analysed using SAS and STATA software. Patients with symptoms of HF that are referred to Echo via the CDR will be classed as Test disease present and the remaining patients classed as Test disease absent. The Observed disease present or absent will be determined by the expert panel following Echo and other clinical assessments. Crosstabulation of Test versus Observed disease status will enable calculation of sensitivity (true positive rate), specificity (true negative rate), positive predictive value (PPV: proportion with a positive test result who actually have the target condition), negative predictive value (NPV: proportion with a negative test result who do not have the target condition), and likelihood ratios for testing the performance of the CDR. 95% confidence intervals for these performance statistics will be calculated using the binomial exact method.

To confirm whether the NT-proBNP cut-offs in the CDR are optimal in the real life clinical setting, an additional ROC curve analysis of NT-proBNP to predict HF will be performed. Analysis will compare the CDR performance against the step 1 reference test alone; against the step 1 reference test plus clinical features of the CDR (step 2); and against the step 1 reference test plus the CDR and the NT-proBNP result (the reference standard, step 3). Step 3 is the primary reference standard for analysis. This will allow us to: 1) quantify the effects of any incorporation bias; 2) explore the impact that availability of NT-proBNP test result would have on the reference standard diagnosis of HF. Comparison of the GPs’ and researcher’s clinical findings (lung crepitations, ankle oedema, decision to refer to Echo) will be assessed by the kappa statistic. Logistic regression will be used to identify which diastolic parameters of echocardiography are independently associated with the diagnosis of heart failure with preserved ejection fraction.

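### The lower NT-proBNP cut-off for women with ankle oedema (190 pg/ml) is out of line with the rule's five other BNP/NT-proBNP pairs and should be checked against its source

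*Protocol article*

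**What the plan says.** The Clinical decision rule section of the protocol article sends some patients straight to echocardiography on clinical features alone. The rest have a natriuretic peptide test, with a cut-off that depends on sex and ankle oedema. Each of the three strata has a BNP range, with an NT-proBNP range in brackets as the alternative:

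- "Female without ankle oedema, refer if BNP > 210-360 pg/ml depending upon local availability of echocardiography", with the bracketed alternative "or NT-proBNP > 620-1060 pg/ml"
- "Male without ankle oedema, refer if BNP > 130-220 pg/ml (or NT-proBNP > 390-660 pg/ml"
- "Female with ankle oedema, refer if BNP > 100-180 pg/ml (or NT-proBNP > 190-520 pg/ml"

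The cut-offs appear nowhere else in the article.

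Three other statements decide what these numbers do in the study. The assay is NT-proBNP: the Blood collection and biomarker assessment section plans to "perform a point of care NT-proBNP test using a Cobas h 232 Reader". The Statistical analysis section turns the rule into the index test result: "Patients with symptoms of HF that are referred to Echo via the CDR will be classed as Test disease present". The Background says that "GPs will not apply the CDR", so the rule classifies patients in the analysis and does not steer referral during the study.

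**The concern.** The two assays are set side by side as alternatives within each stratum, so a steady relation between the columns is expected. Five of the six pairs show one. The lower limit for women with oedema does not, and the article gives no reason for the exception.

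The bracketed column is the one the study can apply, and the CDR result feeds the sensitivity, specificity and predictive values that form the first primary outcome. A wrong figure here would mean that part of one stratum is classified by a cut-off other than the one intended for validation. The direction is known: a limit that is too low makes more women test positive. Those with heart failure (HF) would be added to the true positives and those without to the false positives, so sensitivity could rise and specificity fall.

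**Working it through.** **Inputs.** All six pairs come from the Clinical decision rule section. Total sample size (500) and HF prevalence (30%) come from the Sample size section.

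**Check 1: NT-proBNP divided by BNP, in pg/ml.**

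| Stratum | Lower limits | Upper limits |
|---|---|---|
| Women without oedema | 620/210 = 2.95 | 1060/360 = 2.94 |
| Men without oedema | 390/130 = 3.00 | 660/220 = 3.00 |
| Women with oedema | **190/100 = 1.90** | 520/180 = 2.89 |

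The other five ratios run from 2.89 to 3.00, with mean 2.96.

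**Check 2: upper limit divided by lower limit.**

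| Stratum | BNP | NT-proBNP |
|---|---|---|
| Women without oedema | 360/210 = 1.71 | 1060/620 = 1.71 |
| Men without oedema | 220/130 = 1.69 | 660/390 = 1.69 |
| Women with oedema | 180/100 = 1.80 | **520/190 = 2.74** |

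**Check 3: women with oedema relative to men without oedema.** At the upper limits the assays agree: BNP 180/220 = 0.82, NT-proBNP 520/660 = 0.79. At the lower limits they do not: BNP 100/130 = 0.77, NT-proBNP 190/390 = 0.49.

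**Could rounding explain it?** Suppose every figure was rounded to the nearest 10 and so may be off by 5 either way. The disputed ratio could then lie between 185/105 = 1.76 and 195/95 = 2.05. The smallest value that any other pair could take is 515/185 = 2.78. The intervals do not meet.

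**Size of the discrepancy.** Applying the range of the other ratios to BNP 100 gives 100 × 2.89 = 289 to 100 × 3.00 = 300 pg/ml. Dividing the row's own upper limit by its BNP range ratio gives 520/1.80 = 289 pg/ml. Read the other way, NT-proBNP 190 would pair with a BNP between 190/3.00 = 63 and 190/2.89 = 66 pg/ml, not 100. This arithmetic measures the gap and says nothing about which threshold is clinically right.

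**Effect per patient.** Expected HF patients: 0.30 × 500 = 150. Without HF: 350. One woman with HF whose test status changes moves sensitivity by 1/150 = 0.67 percentage points. One without HF moves specificity by 1/350 = 0.29 points.

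**Effect on the sample size.** None. The stated precision follows from the planning values alone: 1.96 × √(0.94 × 0.06/150) = 3.8 points for sensitivity (stated as within 4) and 1.96 × √(0.48 × 0.52/350) = 5.2 points for specificity (stated as within 6).

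**The case against.** The strongest reply is that nothing in the article says the NT-proBNP limits were obtained by multiplying the BNP limits. They are offered as alternatives and may have been derived separately; only the derivation report could settle it, and it is not at hand. This stands. The misfit is a fact, but the mis-statement is an inference.

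A reader might infer that 190 is the figure the primary analysis will use. The article does not support that. It gives ranges, with a remark in the first row that ties the choice to local echocardiography availability, and it does not say that the lower limits are the operating point. At the upper limit the figure is 520, which fits the pattern.

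A reader might also infer that the planning values came from a different rule. The Sample size section says only: "Calculations are based on sensitivity of 94% and specificity of 48% obtained from application of the CDR". It does not say which assay or which end of the ranges produced them, so no link to the 190 can be shown in either direction.

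The possible harm is also limited. The affected group is narrow, and its size is not given. GPs do not apply the rule, and NT-proBNP, echocardiography and the panel diagnosis are planned for every participant. Neither referral nor verification within the study therefore depends on 190, and CDR status can be recomputed.

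The planned ROC analysis of the NT-proBNP cut-offs does not answer the point. It asks whether the stated cut-offs perform best, takes them as the point of comparison, and would not reveal a copying error.

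**Conclusion.** The inconsistency is real: one of six pairs breaks a pattern that the other five keep, on three separate comparisons, by more than rounding allows. A mis-statement is probable but not proven.

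The consequence is conditional. If the lower end of the range is the operating point and 190 is wrong, the women at risk of misclassification have ankle oedema, no history of myocardial infarction, no basal crepitations, and NT-proBNP between 190 and roughly 290-300 pg/ml. The cost is 0.67 points of sensitivity or 0.29 points of specificity for each of them, assuming the planned 150 and 350 patients. The total shift cannot be stated without the size of that group. If the upper end is used, no patient's status changes.

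The point deserves settling because the figure is a decision threshold of the primary index test and the check is cheap.

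**What to change.** Before any CDR status is computed, reconcile the 190 pg/ml figure with the sponsor's own derivation output for the rule. If it is a transcription error, correct the Clinical decision rule section. If it is confirmed, add a sentence saying why this pair departs from the other five.

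Reporting accuracy under a second cut-off read off the other ratios is not recommended: the documents supply no such threshold, and it would put an extrapolated referral limit into the primary analysis.

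The cost is one look-up and either one corrected number or one added sentence. Sample size, data collection and patient contact are unaffected.

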### Primary and secondary endpoints

Primary outcomes include:

• Test performance of the CDR, estimating the sensitivity and specificity, positive predictive value and negative predictive value of the CDR for diagnosis of HF in symptomatic patients presenting with shortness of breath, lethargy, or ankle oedema of over 48 hours duration

• Test performance of the diagnostic accuracy of NT-proBNP for diagnosis of HF in symptomatic patients, including sensitivity, specificity, positive predictive value and negative predictive value

• Proportion of patients with LVSD or not (ejection fraction <40%) and HF or not

Secondary outcomes include:

• Combination of the CDR and NT-proBNP

• Modelling of CDR test performance and epidemiological data to ascertain the most cost effective strategy in the diagnosis of HF in primary care, incorporating data on quality of life (EQ-5D and SF12 questionnaires), clinical events and health care resource use

• Reliability of GP clinical judgment alone in diagnosing HF

• Reliability of individual clinical features

• Reliability of ECG interpretation

• Estimation of the best performing cut-offs for NT-proBNP to maximise diagnostic yield and for maximizing cost-effective referrals

• Determine the use of variable echocardiographic markers of diastolic function in the diagnosis of HF with preserved ejection fraction

### Clinical judgment

During the initial consultation, GPs will have identified a patient as eligible for referral to one of the two research assessment clinics (i.e. recent new onset shortness of breath, lethargy or ankle oedema of over 48 hours duration). They will then complete the two clinical judgment sections of the online web-based Case Report Form: 1) details of symptoms, history and patient information, including the predictive clinical features of the CDR; 2) whether they would have made a clinical diagnosis of HF or not and what they would have done routinely with this patient (i.e. investigate, initiate referral, treat, follow-up). Following diagnostic assessment at the research assessment clinic, the NP results will be fed back to GPs and based on those results, GPs will be asked what they would do (refer or not refer to Echo) and if they would amend their original diagnosis.

### Diagnostic assessment

The GP will have arranged for all patients to receive a chest x-ray when verbally consenting patients for referral (as is usual practice). Within seven days of referral, the research assessment clinic team will obtain written informed consent, collect baseline demographics, administer quality of life questionnaires (EQ-5D [44] and SF12 questionnaires [45]), clinically assess patients, perform an ECG and echocardiogram, and take blood for NT-proBNP, along with creatinine for a renal dysfunction test, calculating an eGFR (serum profile). These clinical assessments will be made by a research nurse or clinical research fellow trained in these assessments, including phlebotomy, auscultation and chest examination. The heart sounds and chest sounds for each patient will be recorded digitally and a random sample validated by a Senior Cardiologist blinded to the assessment clinic findings. If the research team believes an early decision on management needs to be taken on the basis of the patient’s symptoms or signs at the research assessment clinic, or the results of any of the investigations, an urgent specialist referral will be organised via the patient’s GP. After we have received the GPs’ clinical judgment in the Case Report Form on what they would do (refer or not refer to Echo), all test results will be made available to GPs.

### ECG assessment and interpretation

A 12-lead electrocardiogram (ECG) will be performed. ECGs will be analysed with diagnostic software and double reported and interpreted by the Echocardiographic Technician and a blinded consultant cardiologist, blinded to each other’s interpretation, the software interpretation and other data (i.e. symptoms, echocardiography, chest x-ray, NT-proBNP results). Inter-observer variability will be recorded and analysed.

### Echocardiographic assessment

Echocardiography will be performed within seven days of GP referral by a BSE Accredited Echocardiography Technician, using a portable high-quality Vivid i Ultrasound machine. The echocardiographic assessment, with objective assessment of left ventricular dimensions and ejection fraction, measurement by an area-length method, will be extended to include assessment of diastolic dysfunction. Echocardiogram results, together with clinical assessment results, will be used to establish the final diagnosis, as the reference standard.

### Questionnaire measures

The quality of life questionnaires will be self-administered in the research clinic and data entered into an electronic database. Follow-up questionnaires will be mailed to patients at 6 and 12 months to provide data for health economic modelling. We shall register participants with the Office of Population & Census Statistics (OPCS), based on our previous studies (e.g. Echoes-X), and the research team will check patient status (dead/alive) before sending follow-up questionnaires to patients.

#### The EuroQol 5D (EQ-5D) questionnaire

The EQ-5D is a widely used patient-based generic questionnaire for self perceived health assessment [44]. There are five domains, including mobility, self care, main activity (i.e. work), leisure activity, pain and anxiety. It describes health-related quality of life, giving a single index score for each health state measured that can be combined to generate a single index where 1 = perfect health and negative scores represent poorer states of health.

#### SF-12 questionnaire

The SF-12 is a widely used and validated short generic questionnaire for measuring health related QoL [45], and has been validated for measuring QoL of patients with cardiovascular disease [46].

### Blood collection and biomarker assessment

We shall collect a 30ml blood sample by venepuncture into EDTA K2 blood tubes to perform a point of care NT-proBNP test using a Cobas h 232 Reader and Roche Diagnostics CARDIAC proBNP test strips, for immediate results, and to perform a serum creatinine test to exclude renal dysfunction and calculate an eGFR (serum profile). Blood samples will be sent to Midlands Pathology for spinning and storage for batch analysis, and stored at −80°C for future analysis.

